### Sample size calculation

The required sample size of 360 patients (180 patients per arm) is based on the following assumptions:

1) A clinical response (a clinically meaningful improvement of at least 4 points [19]) of 50% in the treated arm versus 30% in the control arm [24,25] (implying an effect size *d* = 0.42 for the clinical response), and a power of 80% to detect a difference in the clinical response rate of the primary outcome between the treated and control arm with a two-tailed alpha of 5%. This assumption gives a sample size of 180 patients in total (90 patients per arm), ignoring at first the design effect due to clustering of patients within physicians.

2) The number of participating GPs will be about twice as large as the number of pulmonologists.

3) An estimated availability of 5 patients per GP and 8 patients per pulmonologist on average. This, together with assumptions 1 and 2, gives a total of 20 GPs and 10 pulmonologists. However, the following three steps result in a sample size which is twice as large, that is 40 GPs and 20 pulmonologists.

4) An intraclass correlation coefficient (ICC) of 0.05, meaning that about 5% of the total outcome variation within each arm is between GPs and between pulmonologists, instead of between patients of the same physician. Literature suggests that an ICC of 0.05 is a good default value for trials in primary care [26-28]. Combined with assumptions 2 and 3, and allowing for 10% more clusters (healthcare providers) to compensate the power loss due to variation in cluster size, that is, in number of patients included per healthcare provider, this ICC of 0.05 implies a design effect of 1.38 [29]. The number of clusters must thus be multiplied with 1.38.

5) A dropout rate of 25% of patients and/or clusters, to be compensated by multiplying the number of clusters to be included by 1.33 (since 75% of 1.33 is 1). Dropouts will be included into the analyses (intention to treat), but contribute less to the power due to missing data, hence the present correction.

6) Data analysis of the primary outcome with the recommended PQL2 (penalized quasi-likelihood) estimation method which requires a further multiplication of the number of clusters with a factor of 1.10 [30].

Combining assumptions 4, 5 and 6 gives a multiplication factor of 1.38 * 1.33 * 1.10 = 2 for the number of GPs and pulmonologists as computed in steps 1 to 3, leading to the planned sample size of 40 GPs, 20 pulmonologists and 360 patients in total.

### Statistical analysis

All baseline variables and outcomes will be summarized with descriptive tables and, in the case of repeated measures, plotted against time per treatment arm.

The primary and first two secondary outcomes are binary outcomes and will be analysed with mixed logistic regression, using PQL2 or numerical integration as method of estimation.

All quantitative outcomes will be analysed with mixed linear regression, with physician, patient and measurement as three levels at which sampling error occurs, and as predictors treatment arm, time point of measurement, treatment by time interaction, patient demographics and other prognostic variables. Generalized linear mixed models with negative binomial distribution will be used to estimate the adjusted difference in exacerbations. Costs will also be analysed with generalized linear mixed models using a log-normal distribution or gamma distribution. A p-value of < .05 will be considered statistically significant.

All data will be analysed according to the intention-to-treat principle, including all randomised healthcare providers and patients. To prevent missing data, patients will receive reminders for the questionnaires if they do not return the questionnaire within three weeks. If necessary, multiple imputation to cope with missing values will be used [31].

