### Selection, recruitment and randomisation

This study will take place in general practices and hospitals throughout the Netherlands. The researchers will contact general practitioners (GPs) and pulmonologists using a GP network (CAHAG; COPD and Asthma GP Advice Group) and the pulmonologists association (NVALT; Dutch Association of Physicians for Lung Diseases and Tuberculosis). To avoid contamination of care (i.e. patients from the control group receiving the intervention because they are treated by the same caregiver), it is vital that the randomisation between the groups takes place at caregiver-level and not at patient-level. Therefore, healthcare providers will be randomly assigned to intervention or control group in a 1:1 ratio with the help of a computer program designed by the Maastricht University Centre for Data and Information Management (MEMIC). Randomisation will be stratified by type of caregiver (GP or pulmonologist) and variable blocks of two, four or six will be used to make sure there are an equal number of caregivers from primary and secondary care in the intervention and control group. The researcher will enter the names of the healthcare providers into the computer program, which will then randomly allocate them to either the intervention or control group.

Participating healthcare providers will be asked to invite patients from their listed patient databases to participate in the trial. Patients that meet the inclusion criteria and exclusion criteria (see next paragraph) will be sent an information letter including an informed consent form. Healthcare providers will also directly invite patients to participate if they see them during consultations. If the patient agrees to participate in the study, an appointment will be made with the healthcare provider to discuss further details of the trial, recheck whether the patient is eligible for the study and sign the informed consent form.

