### Outcomes

#### ***Primary outcome***

The primary outcome measure will be the proportion of patients in the intervention group with a clinically meaningful improvement on the SGRQ [19], that is, a decrease of at least 4 points between baseline and 18 month follow-up, compared with the control group.

The SGRQ consists of 50 questions with scores that range from 0 (best) to 100 (worst). Higher scores indicate more advanced impairment in health-related quality of life [12].

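### The primary responder model names neither caregiver type nor baseline SGRQ; followed as written, it leaves baseline imbalance in the comparison and gives up modest power

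*Protocol article*

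**What the plan says.** - **Primary outcome** (Primary outcome): a responder is a patient with "a decrease of at least 4 points between baseline and 18 month follow-up, compared with the control group".
- **Primary model** (Statistical analysis): the primary outcome, like the first two secondary ones, "will be analysed with mixed logistic regression, using PQL2 or numerical integration as method of estimation". No fixed effects are given.
- **Quantitative outcomes** (same section, next paragraph): the predictors are "treatment arm, time point of measurement, treatment by time interaction, patient demographics and other prognostic variables". For exacerbations, an adjusted difference is promised.
- **Design** (Selection, recruitment and randomisation): "healthcare providers will be randomly assigned to intervention or control group in a 1:1 ratio", and "Randomisation will be stratified by type of caregiver (GP or pulmonologist) and variable blocks of two, four or six will be used". The same caregivers then invite patients from their own lists.
- **Sample size** (Sample size calculation, item 4): the ICC of 0.05 is described as "about 5% of the total outcome variation within each arm is between GPs and between pulmonologists".
- **SGRQ score** (Secondary outcomes, item 3): the comparison is the absolute difference at 18 months, not the change from baseline.

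Table 1 schedules the SGRQ at baseline in both arms, and caregiver type is known at randomisation. Both variables are therefore available.

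**The concern.** A responder defined by change is not protected against baseline imbalance. Patients who start worse tend to regress towards the mean and so cross the 4-point threshold more often, and a patient who starts below 4 cannot respond at all. If one arm enrols patients with worse scores, part of the responder difference reflects the starting point and not the tool. Such imbalance is plausible beyond chance. Caregivers are the randomised units, they invite their own patients, and only intervention caregivers receive the tool, so those who recruit may know their arm.

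Caregiver type is the only stratification factor and separates primary from secondary care. A model that leaves it out assigns any care-type difference in response to the provider variance.

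A related problem affects the 18-month SGRQ score. If baseline is one of the modelled time points and the arms are free to differ there, the 18-month contrast contains the baseline gap.

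**Working it through.** **1. The plan's own figures.** With d = 0.42, 80% power and two-sided 5%, n = 2 × (1.96 + 0.842)² / 0.42² = 89 per arm. The unpooled two-proportion formula for 50% versus 30% gives (1.96 + 0.842)² × (0.25 + 0.21) / 0.20² = 90 per arm, hence 180 in total. The design effect is (1 + 5 × 0.05) × 1.10 = 1.375, stated as 1.38. The product 1.38 × 1.33 × 1.10 is 2.02, and 180 × 2.02 is about 363, against the stated 360. The figures reproduce, and none of them depends on covariates.

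**2. Baseline imbalance and the responder difference.** Assumptions not in the documents: baseline-to-18-month SGRQ correlation r of 0.7 to 0.9, and intervention patients 0.2 or 0.4 SD worse at baseline. Take no treatment effect and 30% response in controls. The worse-starting arm falls by an extra (1 − r) × imbalance, and the SD of change is √(2(1 − r)) in SD units. The spurious difference is Φ(−0.524 + (1 − r) × imbalance / √(2(1 − r))) − 0.30.

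| r | 0.2 SD | 0.4 SD |
|---|---|---|
| 0.9 | 1.6 points | 3.2 points |
| 0.8 | 2.2 points | 4.5 points |
| 0.7 | 2.7 points | 5.6 points |

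This was also simulated with a random-intercept logistic model fitted by quadrature: 40 providers of 5 patients and 20 of 8, 25% dropout, latent ICC 0.05, 300 runs per setting. With no treatment effect, the unadjusted test rejected in 6% to 15% of runs. Adding caregiver type alone changed this little. Adding baseline SGRQ as well brought it to 4% to 7%.

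**3. How large is a chance imbalance?** If the planning ICC also applies to baseline SGRQ, the SE of the baseline difference is √(2/180 × 1.25) = 0.118 SD. An imbalance of 0.2 SD is then 1.7 SE, reached in either direction by chance in about 9% of trials. An imbalance of 0.4 SD is 3.4 SE and would need selective recruitment.

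**4. Power with balanced arms.** Same simulation with 50% versus 30%, 600 runs per setting, a caregiver-type log odds ratio of 0 or 0.5, and baseline SGRQ 0.5 SD apart between care types (the last two are assumptions).

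| Model | Power | Log odds ratio | SE |
|---|---|---|---|
| Arm only | 85–88% | 0.87–0.92 | 0.287–0.306 |
| + caregiver type | 86–89% | 0.88–0.92 | 0.283–0.290 |
| + caregiver type and baseline SGRQ | 87–92% | 0.91–1.02 | 0.294–0.309 |

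Setting by setting, the full model gains 2 to 6 points (Monte Carlo error of each power about 1.4 points).

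**5. Caregiver type and the provider variance.** The planned patients split 200 to 160, or 5/9 to 4/9. At an average response of 40%, a care-type difference Δ adds (5/9)(4/9)Δ²/0.24 to the apparent ICC: 0.010 for Δ = 0.10 and 0.041 for Δ = 0.20 (both assumed). The apparent design effect 1 + 5 × ICC goes from 1.25 to about 1.30 or 1.46. The standard error then rises by √(1.30/1.25), about 2%, or √(1.46/1.25), about 8%.

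**6. The 18-month SGRQ score.** In a model with arm, time and arm-by-time, the 18-month contrast is the baseline gap plus the difference in change. With no treatment effect and regression to a common mean, the part that remains is r × gap: from 0.7 × 0.2 = 0.14 SD to 0.9 × 0.4 = 0.36 SD. At an assumed SD of 18 this is 2.5 to 6.5 SGRQ points. It runs against the arm that starts worse, whereas the responder shift favours that arm.

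**The case against.** The strongest objection is that this is a condensed article. It does not say that the primary model is unadjusted. The sentence on the logistic model does not name even the treatment arm, so it is plainly shorthand, and a full protocol or analysis plan may hold the covariates. That stands against any claim that the trial will run an unadjusted primary analysis, which a reader might infer but the text does not support. It does not remove the point: the article fixes predictors for other outcomes, and neither of the two most relevant variables appears by name anywhere in the analysis.

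Other stronger readings also fail:

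- **Adjustment would shrink the standard error.** It does not with both covariates. The power gain comes from a larger conditional log odds ratio.
- **Omitting caregiver type biases the result.** Stratified blocks already balance it, so the effect is only a conservative interval.
- **The power calculation assumes that type is adjusted for.** The ICC wording can be read as variation within type, but the article does not say so.
- **CAT carries the same baseline gap.** It is defined as a difference from baseline, so it does not.
- **PQL2 should be excluded.** The plan allows for PQL2 in its sample size, and preferring one estimation method is a matter of choice.

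It is also fair that chance imbalance is covered by the error rate of an unadjusted test, and that selective recruitment may act through factors that baseline SGRQ does not capture. Adjustment reduces this risk without abolishing it. The broad mention of prognostic variables for the quantitative outcomes could include caregiver type, but it does not settle how baseline is handled.

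**Conclusion.** The point holds as a worthwhile improvement to the plan, not as a demonstrated error. Followed as written, the primary comparison gives up about 2 to 6 points of power. An imbalance of 0.2 to 0.4 SD in baseline SGRQ would move the response difference by about 1.6 to 5.6 points, against the 20 planned. The upper end requires selective recruitment, which the design makes possible. Leaving out caregiver type costs some interval width, about 2% to 8% in standard error if response differs by 10 to 20 points between care types, and causes no bias. The 18-month SGRQ score difference is exposed to a baseline gap if baseline is modelled as a time point with the arms free to differ.

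These sizes rest on assumed correlations, imbalances and care-type differences that the article does not give. A reader might infer that the trial is underpowered. It is not: the stated sample size reproduces, and the simulated arm-only analysis exceeds 80% power.

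**What to change.** State the primary model, and the 6- and 12-month responder models, as arm + caregiver type + continuous baseline SGRQ with a random intercept for provider. Say that the odds ratio is conditional on these covariates as well as on provider, and report a marginal risk difference beside it if a population-level figure is wanted. For the SGRQ score, include caregiver type and either constrain the arms to a common baseline mean or use baseline as a covariate.

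This takes a few sentences in the analysis section, settled before outcome data are seen. No new data are needed and the sample size does not change. The one small drawback is that the odds ratio becomes conditional on the added covariates and is not directly comparable with an unadjusted one.

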## Discussion

This paper describes the design of a cluster RCT to evaluate the effectiveness of the newly developed ABC tool. The development of the tool was based on the insight that the severity of COPD has to be determined by both the severity of the airway obstruction and the burden of disease. The 2014 guidelines of the Global Initiative for Chronic Obstructive Lung Disease (GOLD), recommend a comprehensive symptom assessment in determining the severity of COPD [17]. The guidelines also introduced a combined COPD assessment resulting in an ABCD classification. This novel classification integrates symptom severity as measured by mMRC [32], CCQ [11] of CAT [20], versus prognostic indicators of pathophysiologic severity assessed by airflow obstruction and exacerbation history [33]. The ABC tool offers a different operationalization of this new approach and goes beyond classification. The strength of the tool is that it provides a profile of scores on many different domains of COPD-related health. The tool not only focuses on the quantification of the burden of COPD, but determines the actual integrated health status. In addition, it provides a treatment algorithm which gives the patient and healthcare provider insight into treatment options accordingly. The tool offers a visual display of the integrated health status using balloons to show the scores on the different domains of the ABC scale and additional items such as smoking status and exacerbation history. Furthermore, the algorithm provides treatment advice, including pharmacologic options as well as non-pharmacologic options, to formulate a personalized treatment goal and treatment plan. The tool is designed to provide insight into the patient’s individual burden of COPD and therefore enables to make a tailored treatment plan and to make the patient feel co-responsible for their own treatment, using principles of shared decision making [13].

An important issue during the process of designing the study was the selection of an appropriate primary outcome measure. It is more common to use objective parameters, such as the airway obstruction, as primary outcomes [34]. However, airway obstruction is hypothesized to correlate poorly with health status and/or quality-of-life [4]. We therefore decided to use a health-related quality-of-life questionnaire. Since treatment in the intervention arm is based on the outcomes of this new instrument, which is based on the CCQ, a different quality-of-life instrument will be used to measure the primary outcome. We decided to use the SGRQ [12], a disease-specific quality-of-life instrument. We hypothesize that the use of the ABC tool in daily care will have a positive effect on the quality-of-life of COPD patients As the CAT is part of the assessment according to the GOLD guidelines [17], we decided to use it as a secondary outcome measure.

The trial will be conducted throughout the Netherlands, in both primary and secondary care. This will make it possible to evaluate the effectiveness of the ABC tool on the health status of patients with different COPD severities. Conducting the study in many clusters throughout the Netherlands might lead to a higher external validity of the results. Furthermore, it might help facilitating the process of implementation. If the results of this trial are as expected, it will be advised to implement the ABC tool in routine care. To facilitate this, it is recommended to adopt the tool in the registration systems of healthcare providers and in healthcare standards. Using the tool in routine care provides structure in each consultation, and more insight for patients in all factors related to COPD. It might help healthcare providers to discuss difficult issues with their patients related to COPD, such as emotions, smoking cessation and impact of COPD on daily life. Furthermore, it might lead to more commitment of the patient and taking the lead in their own treatment, increasing their self-management.

## Abbreviations

ABC scale/tool: Assessment of Burden of COPD scale/tool; CAT: COPD Assessment Test; CCQ: Clinical COPD Questionnaire; COPD: Chronic Obstructive Pulmonary Disease; DALY: Disability Adjusted Life Years; EQ5d-5 L: EuroQol5d-5 level Questionnaire; FEV1: Forced Expiratory Volume in one second; GP: General Practitioner; mMRC: modified Medical Research Council; NVALT: in Dutch: Nederlandse Vereniging van Artsen voor Longziekten en Tuberculose; PACIC: Patients Assessment Chronic Illness Care questionnaire; PQL: Penalized Quasi-Likelihood; RCT: Randomised Controlled Trial; SDM: Shared Decision Making; SGRQ: The Saint George Respiratory Questionnaire; VAS: Visual Analogue Scale.
